## Experimental products or medical devices tested

No experimental products will be administered to participants, and no medical devices will be tested in the context of this study.

# VIGILANCE

## Definitions

An **adverse event** is defined as an unwanted occurrence in a person who participates in interventional research, whether or not it is related to the study, or the product to which the study relates.

An **adverse effect** is defined as an undesirable event for which a causal link (even weak) is suspected or can be established with a healthcare product or a medical procedure.

A **serious adverse effect (SAE)** is defined as any event or adverse effect that results in death, endangers the life of the person participating in the study, requires hospitalization or the prolongation of hospitalization, causes significant or lasting disability or incapacity, or results in a congenital anomaly or malformation, and, in the case of a drug, regardless of the dose administered.

A **serious incident** or **risk of incident** corresponds to the involvement of a medical device in an event that has resulted or may have resulted in the death or serious deterioration in the state of health of a patient, user or third party.

A **new fact** is any new data that may lead to a reassessment of the risk-benefit ratio of the study or of the product that is the object of the study, to changes in the use of this product, as the study is conducted, or in documents relating to the study, or to the suspension, interruption or modification of the research protocol or similar studies. In the case of trials involving the first administration to humans, or the use of a health product in people who have no known medical condition, any serious adverse effect is a new fact.

## Safety assessment methods and schedule

No specific parameters will be used to monitor patient safety. In accordance with standard care procedures, investigators must report adverse effects; incidents and the risk of serious incidents that they have identified or suspected throughout the patient’s participation in the study.

## Procedures for reporting adverse effects, incidents or the risk of incidents

As soon as an investigator becomes aware of an adverse effect, an incident or the risk of a serious incident, he or she must report it directly to the relevant authority (see Table below) in accordance with the procedures in force at the establishment, specifying in the report that the patient is included in the POSITION study.

| Event related to: | Health monitoring or agency concerned | Relevant authority |
| --- | --- | --- |
| A drug | Drug safety | Regional Drug Safety Center (Centre Régional de Pharmacovigilance) |
| A blood product | Hemovigilance | Local hemovigilance center (Correspondant local d’hémovigilance) |
| A medical device | Equipment safety | Local equipment safety center |
| A care-related act | No health surveillance.  Direct transmission to → | Regional Health Agency (Agence Régionale de Santé) * |
| A care-related infection | Infection control | Local infection control center |
| A non-drug toxic substance | Toxicovigilance | Poison Control Center (Centre Antipoison) |
| A psychogenic substance leading to addictive behavior or drug dependence | Addiction surveillance | Drug Dependence Assessment Center (Center d’Evaluation et d’Information sur les pharmacodépendances-addictovigilance) |
| Food, a food supplement, adulterated products | Toxicovigilance | Poison Control Center (Centre Antipoison) |

* In the case of adverse effects related to healthcare, including venous samples used in the study, they will only be transmitted to the Regional Health Authority if they meet the criteria set out in the Order of February 20, 2017 relating to the criteria for reporting to the Regional Health Authority alerts collected by members of the regional vigilance and support network [(](https://www.legifrance.gouv.fr/eli/arrete/2017/2/20/AFSP1705441A/jo/texte)https://www.legifrance.gouv.fr/eli/arrete/2017/2/20/AFSP1705441A/jo/texte).

Any report of an adverse effect must state that the patient is participating in the study, and must be recorded in the Case Report Form.

In all cases, the report may be transmitted either via the establishment’s internal reporting system (if applicable), or via the adverse event reporting portal.

https://signalement.social-sante.gouv.fr/psig_ihm_utilisateurs/index.html#/accueil.

This portal forwards the report to the relevant authority, and sends the notifier an acknowledgement of receipt, which can be included in the patient’s file.

In the event of a new fact, the investigator, the person responsible for vigilance, and the sponsor will discuss any safety measures that may need to be implemented, the continuation of the study, and the need to contact the Regional Health Authority.

## Methods and duration of follow-up of participants following an adverse effect

When an adverse effect persists, or an incident has ongoing consequences, including after the study has ended, the investigator will monitor the person participating in the study until the event is considered resolved, and will report any follow-up data to the relevant authority.

## Late emergence of serious adverse effects

If the investigator becomes aware of an adverse effect that occurs after the patient’s follow-up period has ended, he/she will report it immediately to the relevant authority, using the same procedures.

# BIOLOGICAL SAMPLE COLLECTION

Within the framework of the study, we will create a biological collection to meet the stated research objectives, and to be able to carry out other analyses or assays in the light of new facts brought to light by the literature, while the purpose of the study will remain unchanged. Analyses carried out for research purposes will not be used for diagnostic purposes.

The saliva samples that are collected (2 x 2 ml bottles) during inclusion and end-of-study visits will be stored on site at −20°C and then transported under optimal temperature conditions by the investigating team to be stored in the −80°C freezers at IRBA (in a dedicated room, [name]) until they are analyzed.

This will result in a collection of 1,600 samples (2 bottles, 2 measurement times, 400 subjects).

The study’s principal investigator is responsible for saliva sampling.

Each sample will be identified by a code (affixed to cryogenic labels) as follows:

- Subject code: Unit code + Subject number

- Visit number: inclusion visit: Vin; for follow-up visits: V1, V2, V3 and V4; final visit: Vfin. Additional visits will be identified by the code Vadd1, Vadd2, etc., depending on the number of additional visits carried out.

The collection of biological samples undertaken in the context of this study has been declared to the competent authority. After the study has ended, the conservation of the collection of biological samples will be declared to the minister in charge of research and to the director of the Agence Régionale d’Hospitalisation (and submitted to the Institutional Review Board for an opinion if the purpose of the study changes).

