## Secondary endpoints

Criteria for meeting the study’s four secondary objectives are as follows:

- - 1. The first secondary objective comprises two evaluation criteria: 1) self-reported scores on the Postural Awareness Scale (APPENDIX 3) pre- and post-intervention, and at the start of each session; 2) variation in measures of postural balance pre- and post-intervention.
    2. The second objective also comprises two criteria: 1) self-reported scores on Cohen’s Perceived Stress questionnaire (APPENDIX 3) pre- and post-intervention, and at the start of each session; 2) variation in measures of allostatic load in saliva pre- and post-intervention (the corticotropic axis: cortisol, DHEA, oxidative stress; the autonomic nervous system: alpha amylase and chromogranin A).
    3. The evaluation criterion for the third secondary objective will be the correct prediction of the risk of fall injury by the machine learning model.
    4. The evaluation criterion for the fourth secondary objective will be the rate of fall injuries in each of the two groups (POTs *vs.* active control), in the period between the end of the study and the end of the selection course. Information about when each participant left the course will be collected from the physician responsible.

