### Inclusion visit

The inclusion visit will take place the day after the group information session, and before any examinations related to the study. During the visit, the investigator or one of his or her collaborators will ask the participant if they want to take part in the study, and will inform him or her:

- of the objective of the study, and any constraints,
- foreseeable risks and expected benefits,
- that personal data collected during the study will be held and processed digitally, and state his/her rights regarding access, opposition and rectification,
- that samples will be conserved for scientific purposes after the study has ended, and obtain consent.

The investigator, or a colleague will answer any questions the participant may have. The latter will then have 15 minutes to reflect on his or her decision to take part in the study. Formal agreement will be obtained by signing the consent document (three copies).

Any changes to the study that impact either patient care, or benefits, risks and constraints will be presented in a new information document. The same procedure will be used to inform those concerned.

The various copies of the information document and the consent form will then be distributed as follows:

- A copy of the information document and the signed consent form will be given to the participant.
- The original will be held by the investigating medic in a safe place that cannot be accessed by third parties.

A copy of each consent form will be sent to the sponsor or its representative after inclusion or, at the latest, at the end of the study, in accordance with the procedures communicated.

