### Initial evaluation visit

The initial evaluation visit will take place immediately after the inclusion visit for subjects who have given consent to participate. During this visit, the investigator, or one of his or her collaborators, will collect clinical data (age, height, weight and gender), run the BESS, and collect posturography measurements. The participant will then complete a medico-demographic questionnaire, together with questionnaires to measure postural awareness (the Postural Awareness Scale) and perceived stress (Cohen’s Perceived Stress questionnaire). Finally, a 4 ml saliva sample will be collected.

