### End-of-study visit

Participant follow-up will end either: (*i*) on the day following the last session of the POTs or the active control intervention; or (*ii*) the day they leave the course (for whatever reason), if this occurs before the end of the intervention (POTs or active control).

A posturography measurement will be performed by the military medic, or one of his or her assistants, and the participant will complete questionnaires measuring postural awareness (the Postural Awareness Scale) and perceived stress (Cohen’s Perceived Stress). Finally, a 4 ml saliva sample will be collected.

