### Biological parameters

A saliva sample will be collected during the initial evaluation visit, and the end-of-study visit (2 x 2 ml at each visit). These samples will be used to monitor markers of the corticotropic axis (cortisol and DHEA), and the autonomic nervous system (alpha-amylase and chromogranin).

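### Saliva sampling is tied to a visit day but not to a clock window, and no collection time is required, so the uncontrolled pre/post change can be confounded with time of day; the two marker lists also disagree on oxidative stress

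*Protocol*

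**What the plan says.** **Timing of the first sample.** Under Inclusion visit: "The inclusion visit will take place the day after the group information session, and before any examinations related to the study". The initial evaluation follows directly, and saliva is its last step, after the clinical data, BESS, posturography and questionnaires: "Finally, a 4 ml saliva sample will be collected". A day is given, but no hour.

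**Timing of the second sample.** Under End-of-study visit, completers are seen the day after their last session. Others are seen on "the day they leave the course (for whatever reason), if this occurs before the end of the intervention". The Schedule row of the Research Summary ties the early visit to the day of the fall injury instead.

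**Labelling.** Under Biological Sample Collection, each sample is identified by a code with two parts: "Subject code: Unit code + Subject number" and "Visit number: inclusion visit: Vin; for follow-up visits: V1, V2, V3 and V4; final visit: Vfin", with further codes for additional visits. That section gives storage temperatures but no time of collection.

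**Markers.** Secondary endpoints (and the Research Summary) name "the corticotropic axis: cortisol, DHEA, oxidative stress; the autonomic nervous system: alpha amylase and chromogranin A". Biological parameters says the samples will be used for "markers of the corticotropic axis (cortisol and DHEA), and the autonomic nervous system (alpha-amylase and chromogranin". Oxidative stress appears only in the first list.

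**Analysis.** Under Statistical methods and in the Research Summary, the biological stress variables are compared by a paired comparison of means, in the POTs group only.

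**The concern.** The second secondary objective asks whether POTs lower the psychobiological stress response, and its biological part rests on the change in these salivary markers. If a marker varies with time of day, the observed change mixes any real change with the difference in sampling hour between the two visits. A paired test within one group has no control change to subtract. A shift in the usual hour between baseline and final visit would then read as an effect of the intervention, or hide one.

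The exposure is greatest where the final visit is triggered by an unscheduled event, because the hour then depends on the event. Under General logistics, different staff also run the two visits: the coordinating team, helped by unit medical staff, runs the first, and the unit's medical officer or a collaborator runs the last. Nothing in the text makes them work at the same hour.

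Collection conditions belong in the protocol, because a time that was never noted cannot be supplied at analysis. The protocol already recognises the principle: under Para-clinical parameters it requires BESS training and a standard posturography procedure for reproducibility. Saliva collection has no counterpart.

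**Working it through.** **1. The plan's own figure.** Biological Sample Collection states: "This will result in a collection of 1,600 samples (2 bottles, 2 measurement times, 400 subjects". Check: 2 × 2 × 400 = 1,600 bottles, which agrees. That is 400 × 2 = 800 sampling occasions, of which 200 × 2 = 400 fall in the POTs group that is analysed.

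**2. What reaches the paired mean.** Let h1 and h2 be a participant's sampling hours, and let k be the hourly decline of a marker on the log scale. The observed log change is the true change − k(h2 − h1), plus error.
- The mean is shifted by k × mean(h2 − h1). Only a systematic difference between visits causes bias.
- The variance rises by k² × Var(h2 − h1). Random differences cost precision.
- Spread in h1 between participants causes no bias if each h2 matches its own h1.

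**3. Illustrative size for one sample.** The documents give no time-of-day effect. Assume cortisol falls 4- to 10-fold over 14 waking hours.
- k = ln(4)/14 = 0.099 per hour, to k = ln(10)/14 = 0.164 per hour.
- Taken 1 hour later: 1 − exp(−0.099) = 9%, to 1 − exp(−0.164) = 15% lower.
- Taken 3 hours later: 1 − exp(−0.297) = 26%, to 1 − exp(−0.493) = 39% lower.

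**4. Sensitivity of the planned test.** Inputs from the sample-size section: 200 in the POTs group and 10% drop-out, so 200 × 0.90 = 180 to 200 pairs; two-sided 5% level. Let d be a systematic time-of-day shift in SD units of the paired difference (assumed), with no true effect. The chance of a significant change is Φ(d√n − 1.96) + Φ(−d√n − 1.96).

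| Assumed d | n = 180 | n = 200 |
|---|---|---|
| 0 | 5% | 5% |
| 0.05 | 10% | 11% |
| 0.10 | 27% | 29% |
| 0.20 | 77% | 81% |
| 0.30 | 98% | 99% |

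A shift of about 0.20 to 0.21 SD is enough for an 80% chance of a significant result.

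**5. How many final samples could be event-driven.** The planning fall rate in the POTs group is 35%, and 0.35 × 200 = 70. On the Research Summary's rule (day of the fall injury), up to about 70 final samples could be unscheduled. On the End-of-study visit rule (day of leaving, for any reason), the number is unknown.

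**6. Marker lists side by side.** The endpoint has five items: cortisol, DHEA, oxidative stress, alpha-amylase and chromogranin A. The measurement list has four: cortisol, DHEA, alpha-amylase and chromogranin.

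**The case against.** The strongest reply is that the label code is an identifier, not a collection log. A paper case report form exists but its fields are not shown, the visit table and schedule figure are not legible in the available text, and posturography files from the same visit may carry a time stamp. This stands. A reader might infer that clock time is lost for good, but the documents support only that the protocol text does not require it to be recorded.

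A reader might also infer that candidates are examined one after another, so that baseline hours must spread over the working day. No section says so. Several unit staff assist, and paper questionnaires and saliva collection could run in parallel. Even a wide baseline spread would not by itself bias a paired mean (step 2 of the working).

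Third, it is tempting to add that a difference in sampling hour between the control year and the POTs year distorts the result. The planned saliva analysis does not compare the two groups, so that difference does not enter it.

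Finally, the missing assay might be read as making the endpoint impossible to complete. Biological Sample Collection says the collection serves the stated objectives and allows further assays, so oxidative stress is not excluded. The two lists simply disagree.

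None of this answers the main point: the text gives no window, no recording requirement, and no control comparison to absorb a shift.

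**Conclusion.** The point holds in a limited form. Sampling is fixed to a day or an event, no clock window is set, and recording of the time is not required. With an uncontrolled paired test in the POTs group, a systematic difference in hour between visits can be confounded with a change in stress, and random differences add noise. It would go too far to say that the endpoint does measure time of day: the documents contain no sampling hours and show no actual shift.

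The size is unknown from the documents. The 26% to 39% for a 3-hour delay rests entirely on the assumed cortisol decline and describes a single shifted sample, not the group mean. The table of false-positive chances rests on an assumed d and a normal approximation. No figure is offered for DHEA, alpha-amylase or chromogranin.

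The matter affects a mechanistic secondary endpoint and leaves the primary analysis of fall injuries untouched. It should still be corrected, because the remedy is cheap and times not captured at collection may not be recoverable. Two inconsistencies stand on the text alone: the marker lists differ, and the Research Summary and the End-of-study visit section define the day of an early final visit differently.

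**What to change.** - **Initial evaluation visit and End-of-study visit:** where the final visit is scheduled, take its saliva sample within a stated tolerance of the participant's own baseline clock hour.
- **Biological Sample Collection:** require the collection time on the label or the case report form for every sample, including those from early leavers.
- **Analysis:** use the recorded time to adjust, or to run a sensitivity analysis, for samples outside the tolerance. The details can sit in the statistical analysis plan.
- **Early final visit:** reconcile the Research Summary with the End-of-study visit section on which day applies.
- **Markers:** make the Research Summary and Secondary endpoints agree with Biological parameters on oxidative stress, either by adding the assay to the measurement list or by removing the marker from the endpoint.

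The cost is one time field, one scheduling instruction and a few wording edits, with no extra samples. The drawback is that saliva may sometimes have to be taken apart from the rest of the visit.

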# DATA COLLECTION AND PROCESSING

Any original document or object that can be used to prove the existence or accuracy of data or facts recorded during the study is defined as a source document.

Source documents include Case Report Forms, paper-based questionnaires, and digitized clinical and paraclinical data.

## Data collected

### Clinical parameters

Clinical data collection will be limited to injury history, age, sex, height and weight. These data will be recorded using posturography software.

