| Schedule | The study will consist of the following visits:   - 1 inclusion visit: inclusion interview and written consent - 1 initial assessment visit: self-report questionnaires (medico-biographical, postural awareness (Postural Awareness Scale) and stress (Cohen’s Perceived Stress Scale), clinical and paraclinical posture measurements and saliva collection. - 4 follow-up visits carried out at the start of the POT or active control sessions, consisting of: self-report questionnaires (postural awareness and perceived stress), - there will be 1 additional visit for participants who suffer a fall-related trauma during the course. The participant will complete questionnaires measuring postural awareness and perceived stress, and a posturography measurement will be performed. - 1 end-of-study visit will take place on the day following the last session of the POT or the active control, or on the day of the fall injury if it occurs before the end of the POT or active control intervention. This visit will include: paraclinical measurement of posture, self-report questionnaires (postural awareness and perceived stress) and saliva collection. |
| Number of subjects | The sample should include 200 participants in each of the two groups (POT and active control), making a total of 400 participants. |

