# SCIENTIFIC JUSTIFICATION

## Current knowledge

### Pathology/ health problems and current knowledge

Physical activity and sport play an important role in the military, as they are used to develop and optimize the operational capacity of combatants. In France, *Entraînement Physique Militaire et Sportif* (Physical and Sport Training for the Military) is designed to enable all military personnel to acquire the physical and mental capacities they need to perform their duties (Etat-major des armées - Centre national des sports de la défense, 2011). In addition, the preservation of operational capacity throughout a military career is based, among other things, on the health benefits of sporting activities, notably with respect to the prevention of chronic, stress-related pathologies such as cardiovascular disease and depression (World Health Organization, 2003).

Nevertheless, physical activity and sport can also be the source of acute (sprains, fractures, etc.) and chronic (tendinopathies) musculoskeletal pathologies. In particular, there is a high rate of lower-limb trauma during physical activities in the military context, both among young enlisted personnel [15–20%] (At, 2016; Bauvent, 2014; Pleche, 2018) in operational military units or during selection courses for specialized units [30–45%] (Bertrand, 2016; Brocard, 2014; Chipault, 2016; Longin, 2015; Morinière, 2013). In addition to their impact on the health of combatants, these injuries have a negative impact on the operational capability of forces (due to incapacity) and a significant economic cost (Ressort, Desjeux, Marsan, & Thevenin-Garron, 2013)

Identifying risk factors is an essential step in developing an injury prevention strategy. Classically, there are two categories of risk factors: (*i*) those that are intrinsic to the individual, and include age, gender, physical condition or tobacco consumption; and (*ii*) extrinsic factors, which relate to the context in which the sporting activity is performed, and which include environmental conditions (temperature, humidity, etc.), the type of activity, or training conditions (progression, regularity, etc.). (Bigard, Cravic, & Banzet, 2010; Meeuwisse, 1994; Williams, 1971). The identification of modifiable risk factors (i.e. those that are amenable to an intervention that will reduce the likelihood of injury), remains a major challenge in the field of sport (Bahr & Holme, 2003).

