## Randomization

There will be no randomization (POTs versus active control) at the individual level (i.e., for each participant in each military unit). This is not possible due to the risk of participants in the POTs group influencing those in the active control group (contamination bias). The conditions under which the selection course is carried out mean that participants in both groups are in close contact with each other. Moreover, it is possible that running the two interventions at the same time may undermine the desired team cohesion. Hence, we have chosen to carry out the study over two successive years (years Y and Y+1):

1. Participants included in year Y will follow the active control program.
2. Participants included in year Y+1 will follow the POTs program.

The order of the two interventions (active control followed by POTs) is deliberately not randomized between units, to ensure that the research protocol is respected throughout the study. If the POTs intervention was run in year Y, and was found to be beneficial, it would be very difficult to expect participating units to set up an active control in year Y+1, as it is unrealistic to expect them to abandon a program with potential benefits for candidates.

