**Analysis of the main objective**

The effect of the intervention (POTs *vs.* active control) on the rate of fall injuries will be evaluated using a comparative survival analysis (the Cox model, with clinical variables as potential confounders). Survival curves for POTs and active control groups will be compared using the log-rank test.

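### Physical condition and tobacco use are named as injury risk factors, but the protocol does not say that either is collected or adjusted for in its non-randomised primary comparison

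*Protocol*

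**What the plan says.** The background on current knowledge divides injury risk factors into extrinsic ones and "those that are intrinsic to the individual, and include age, gender, physical condition or tobacco consumption".

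Under Data collected, the Clinical parameters section states: "Clinical data collection will be limited to injury history, age, sex, height and weight". It adds that these data are recorded through the posturography software.

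The Initial evaluation visit section gives a shorter list: the investigator "will collect clinical data (age, height, weight and gender), run the BESS, and collect posturography measurements". Injury history is not in it. The same section continues: "The participant will then complete a medico-demographic questionnaire". The Research Summary describes what appears to be the same instrument as one of the "self-report questionnaires (medico-biographical, postural awareness (Postural Awareness Scale" and stress questionnaires. Its items are not set out anywhere, and Appendix 3 covers only the postural awareness and perceived stress scales.

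The primary analysis is "the Cox model, with clinical variables as potential confounders", with no variables named.

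On allocation, the Randomization section states: "There will be no randomization (POTs versus active control) at the individual level". It also states: "The order of the two interventions (active control followed by POTs) is deliberately not randomized between units". All six units run the active control in year Y and POTs in year Y+1.

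**The concern.** The two arms are successive intakes, so their comparability is not secured by chance allocation. It depends on the intakes being alike and on adjustment for recorded differences. Of the four intrinsic factors that the protocol itself names, two (age and sex) are on the list of clinical data and two (physical condition and tobacco use) are not.

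If the POTs-year intake is fitter or smokes less, and those factors do affect fall injury, the injury rate falls for reasons unrelated to POTs and the Cox model credits the difference to the intervention. The opposite imbalance would hide a real benefit.

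A statistical analysis plan can choose among recorded variables, but it cannot supply ones that were never recorded. The control arm comes first, so an item missing in year Y cannot be recovered reliably later.

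**Working it through.** **1. Are the factors collected?**

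| Item | Background: risk factor | Clinical parameters | Initial evaluation visit |
|---|---|---|---|
| Age | yes | yes | yes |
| Sex/gender | yes | yes | yes |
| Physical condition | yes | no | no |
| Tobacco use | yes | no | no |
| Injury history | not in this list | yes | no |
| Height, weight | not in this list | yes | yes |

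The medico-demographic questionnaire could fill the gaps, but its content is not stated. The documents therefore establish that the two factors are not named as collected. They do not establish that the factors are uncollected. The same applies to injury history, which may come from the questionnaire; the text does not say.

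**2. The plan's own figure.** Inputs from the sample-size section: 50% v 35%, two-sided 0.05, power 0.80, 10% drop-out, 200 per group. The two-proportion formula with continuity correction gives 183 per group, and 183/0.90 = 204. Without the correction it gives 170, and 170/0.90 = 189. The stated 200 is reproduced to within 3% by the first. With 200 × 0.90 = 180 evaluable per group, power is 0.82. The point made here does not depend on this figure.

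**3. Size of the possible bias.** The documents give no prevalences or effect sizes for either factor, so the inputs here are assumptions. Take one unmeasured binary factor with rate ratio RR for injury, prevalence p0 in the control year and p1 in the POTs year, and no true POTs effect:

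spurious ratio = (1 + p1(RR − 1)) / (1 + p0(RR − 1))

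The planned effect is 35/50 = 0.70, and ln 0.70 = −0.357. The share of the planned effect is ln(spurious ratio)/ln(0.70). The false-positive rate is the two-sided rejection probability of a two-proportion z-test at 0.50 v 0.50 × spurious ratio, with 180 per arm.

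| p0 v p1 | RR | Calculation | Spurious ratio | Share of planned log effect | Two-sided rejection |
|---|---|---|---|---|---|
| 40% v 30% | 1.5 | 1.15/1.20 | 0.96 | 12% | 7% |
| 40% v 30% | 2.0 | 1.30/1.40 | 0.93 | 21% | 10% |
| 40% v 30% | 2.5 | 1.45/1.60 | 0.91 | 28% | 14% |
| 50% v 35% | 1.5 | 1.175/1.25 | 0.94 | 17% | 9% |
| 50% v 35% | 2.0 | 1.35/1.50 | 0.90 | 30% | 16% |
| 50% v 35% | 2.5 | 1.525/1.75 | 0.87 | 39% | 23% |

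This works on the risk scale as an approximation to the Cox analysis, and it gives no credit for partial control through the variables that are collected.

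**4. Could such a factor explain the whole planned effect?** With r = 1/0.70 = 1.43, the E-value is r + √(r(r − 1)) = 2.21. A confounder would need risk-ratio associations of about 2.2 with both year and injury, well beyond the prevalence contrasts assumed above (for example 0.40/0.30 = 1.33).

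**The case against.** A reader might infer that adjustment for fitness and smoking is ruled out altogether, because clinical data are restricted to five items. The documents do not support that. The restriction governs the clinical parameters entered through the posturography software. The self-report questionnaire is a separate source, completed afterwards on paper, and could hold smoking or training items. The Data collected section is also not exhaustive: the caption to the study-schedule figure mentions a fatigue questionnaire that the section omits. The visit table is not visible in the text available.

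Nor is adjustment the only protection. Participants are all selection-course candidates declared medically fit, and the same six units and schedule are used in both years. This narrows differences in physical condition, though it does not remove them and says nothing about smoking.

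The risk-factor sentence is general background on sports injury. It does not show that these factors drive loss-of-balance falls or that they differ between intakes. The sizes above are therefore illustrations, and the milder rows must be reported along with the stronger ones. Some collected variables, such as age, weight and injury history, may also partly stand in for fitness.

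Finally, more covariates cannot separate POTs from calendar year, and the choice of covariates is often left to an analysis plan. Both statements are true. What stands is that the protocol does not say these two items will be recorded, and recording is decided before any analysis plan can help.

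**Conclusion.** The point holds as a gap in stated data collection. The protocol names physical condition and tobacco use as intrinsic injury risk factors, lists neither among its clinical data, names neither as collected elsewhere, and leaves the Cox adjustment variables unnamed. Whether the baseline questionnaire covers them cannot be determined from the protocol. The two sections listing clinical items also differ on injury history.

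If the items are not recorded and the intakes differ, the primary hazard ratio is biased. Under the assumed rate ratios of 1.5 to 2.5 and prevalence differences of 10 to 15 points, the spurious ratio is 0.96 to 0.87, or about 12 to 39% of the planned log effect. The false-positive rate is then about 7 to 23% instead of 5%. A reader might go further and infer that such a factor could produce the whole planned 15-point difference. Under these assumptions it could not do so alone. It could tip a null result into significance or, in the other direction, mask a benefit.

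**What to change.** Before year Y inclusion, amend the Clinical parameters and Initial evaluation visit sections as follows:

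- State the items of the medico-demographic questionnaire. If smoking and training are already in it, say so.
- If they are not, add current smoking and one physical-condition item defined identically in all six units and both years, such as self-reported weekly training hours. A mixture of unit-specific entry tests and training hours would not be one comparable variable.
- List injury history in both sections and give its source.
- Name smoking, the physical-condition item, injury history, age and sex as covariates in the primary Cox model.
- State that this reduces measured confounding but cannot remove confounding by calendar year, because year and intervention coincide in every unit.

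The cost is two questionnaire items at most, a short amendment and a few more model covariates. The questionnaire becomes slightly longer, and no new visit, procedure or staff is needed.
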